***2.2.3 Laboratory and other investigations***

All laboratory results will be filled into a form marked with the participant’s study ID and kept in confidential storage for entering of follow-up results.

**At the study site:**

- All biological specimens will be kept cold and will be transported from the study sites to the US-CDC Bo laboratory (three times weekly during the pilot study) and to Chinese-CDC Jui laboratory at least three times weekly for the main study.

- All sampling and handling of specimens collected for transportation should follow procedures for labeling, packaging, transporting, and storing bio-hazardous material detailed in the operations manual.

**At the Field laboratory (US-CDC BO for Pilot, Chinese-CDC Jui for Main study):**

- For the pilot study, RT-PCR will be performed on all specimens for two viral targets, VP40 and NP, as well as an internal human control, B2M, according to guidelines detailed in appendices 5 and 6. For the main study, conducted at Chinese-CDC, the two RT-PCR gene targets are NP and GP, but the internal control remains the same.

- If the internal human control is negative for a given specimen, this would be viewed as an inadequate sample and a new specimen would be requested.

- Specimens will be stored at -80°C and those that are RT-PCR positive will be shipped to a BSL-4 laboratory for virus isolation testing (US-CDC Atlanta except the semen for the main study), following appropriate protocols for transporting Category I biohazards

- Blood specimens collected during the main study will be tested using an Enzyme Linked Immunosorbent Assay to assess IgG and IgM antibody presence and titers.

**US-CDC Atlanta BSL-4 laboratory:**

- In order to determine if a given body fluid specimen has live virus and is potentially infectious, virus culture will be performed. This can only be safely performed in Biosafety Level (BSL)-4 laboratory conditions, which are not available in Sierra Leone. Therefore specimens which have detectable EBOV RNA by RT-PCR from the pilot study will be transported frozen with adequate safe packaging and cold chain to Atlanta, GA, USA for virus isolation.

- In addition to positive specimen from the pilot study being tested at US-CDC Atlanta, additional virus isolation of body fluids other than semen from the main study will be done in Atlanta.

- For the pilot study, testing for live virus will be performed at the US-CDC BSL-4 laboratory in Atlanta, GA, USA, ideally within 6 months of specimen receipt. Standard EBOV virus isolation protocols for diagnostic specimens will be followed.

- If specimen type and volume permit, the viral titer (TCID50/mL) for the specimen will be determined. This will inform the amount of infectious virus in a specimen, unlike virus isolation which will tell you a binary, (i.e., yes or no) to infectious EBOV virus in the specimen.

- Residual body fluid specimens will be destroyed. Viral isolates, if any, may be preserved at US-CDC for further study in collaboration with MoHS and WHO (in accordance with the research collaboration agreement). Body fluid isolates will be kept in liquid Nitrogen frozen storage (-165oC) in a secure location at US-CDC’s BSL-4 laboratory. Virus isolates can be shared to requesting parties assuming that the requesters can comply with the necessary biosafety requirements (BioSafety Level-4, Select Agent compliance). Further study of virus specimens may include genetic analysis and comparison with other virus strains.

**3. Study instruments**

(See Equipment and Supplies in operations manual)

**4.1 Staffing and work plan**

Staff needed per study site:

- Study supervision: medical superintendent of each hospital where study site located

- Study coordinator: study physician from the hospital

- Three nurses for enrollment, interview, sample collection instruction, HTC

- Lab technician for collection of samples, sample packaging and transport

- Two counselors for pre and post EVD and HIV test counselling: one is a psychiatric nurse and the other is a nurse with a background on training for HIV counselling

- Driver

- Two community liaison officers (Ebola survivors) for community sensitization, recruitment, appointment scheduling

- Two Hygeinists to clean the specimen collection areas and study site
- Research Assistant to enter questionnaire data, generate laboratory line list, and assign Study ID numbers
- HR/ Administration Coordinator
- Data Management Coordinator/Data analyst

***Capacity Building:***

With the exception of the study coordinator and operations manager, both the pilot and main study will be staffed by local staff identified by the implementing partner, with special effort to employ and train Ebola survivors in research skills. Staff will receive training in counselling, community outreach, HTC, data management, research methods, and IPC.

The laboratory partner, Chinese CDC, runs a 2-week capacity building training course for local laboratory staff covering laboratory techniques. As part of this research partnership, Chinese CDC will train and employ local laboratory staff.

**4.2 Administration and monitoring**

The on-site project manager will administer the project under the overall guidance of the PI and partners. The study team may use workflow assignment (or Gantt) charts to help monitor progress. Regular meetings will be held, and progress reports on major results of interviews or analysis will be written at least monthly. Delegated team members will monitor the quality of the data, teamwork output as well as compliance with the project work schedule.

An external monitor, [name], has been invited by the WHO to perform a monitoring visit at the pilot study site in August 2015.

**5. Data quality assurance**

Only trained interviewers and/or lab assistants will be used for the interviews and specimen collection. The topics included in the questionnaires include asking for information that may be perceived as sensitive and efforts will be made to ensure a private setting and calm environment to assure internal validity of the data collected.

Handling and treatment of biological sampling and specimen will follow standard operating procedures. Specimens sent for viral isolation will be handled at appropriate laboratories following relevant protocols for potential biological hazards.

Study staff will review data collected and entered for quality and consistency. Data quality reports will be developed and generated weekly with feedback to study staff at the lab and participating ETU sites.

**6. Data management**

• All MoHS-owned data related to a study participant will be assigned the participant’s unique study ID. No patient-identifying information (i.e., names) will leave Sierra Leone.

• Interview data will be organized in databases stored on secure local servers within the Ministry of Health in Sierra Leone and WHO and will be backed-up regularly. Collected data will be directly recorded on computers or tablets to minimize data recording and entry errors and minimize delays in data availability. If paper forms must be used, interview responses will be entered into the database either daily or as a group at the close of data collection; and 10% of entered forms will be re- checked to identify any problems with data entry accuracy that must be addressed.

• Electronic equipment and files will be kept password-protected.

• Paper forms and electronic devices will be kept locked when not in use.

• All individual data identifying direct patient identifiers will be removed from the dataset before analysis and replaced with a unique participant code that can be linked back to individuals via a master key at a centralized secure server and database.

• Individual records and the key linking the participant code number will be kept secure, accessible only to the local study team under the supervision of the study PI and MoHS in collaboration with WHO, US-CDC and Chinese-CDC.

• Paper interview forms, if used, will be destroyed within one year after all data are entered and verified.

• Laboratory RT-PCR results will be batch processed and complete RT-PCR results for all specimen types will be reported back within 1 week of specimen receipt to each site coordinator. A positive RT-PCR result on any specimen should be entered in the secured data base and reported within 8 hours to the study PI and WHO, US-CDC, Chinese-CDC local coordinators as well as the site coordinator where the specimen was collected.

- Antibody testing will be batch processed and results will not be reported to participants.

• Laboratory staff will identify specimens only by the labelled study ID, and will not have access to any personally identifying information.

• Counsellors will provide laboratory results only in person and only to participants who (1) return for a follow-up study visit; and (2) present their study ID card or confirm their identity and study ID number; and (3) agree to receive their own results. Individual results will not be shared with anyone other than the study participant. Results will be presented according to the counselling script.

• Virus isolation results from US-CDC Atlanta will be reported promptly to the study PI and entered in the secured data base as they arrive. These confirmatory results will not be available within a clinically relevant time frame (6 months). Positive results will be reported to participants.

**7. Data analysis plan**

• Descriptive analysis of the study participants will be performed by the study PI and staff with the support of WHO and US-CDC. WHO and US-CDC technical assistance may be provided as needed for these and any additional analyses of the study data. Any further statistical analysis will be conducted using adequate statistical program packages with the assistance of WHO and US-CDC.

• Viral Persistence time will be measured in days or months from time after symptom onset and will also be presented as time after ETU discharge.

• The primary measures of interest are:

o the period prevalence of viral persistence in 1st/baseline samples (0-3 months, >3-6 months etc)

o survival probabilities over time (based on base-line positive samples)

o maximum duration of tissue culture-positive results for EBOV by number of days since symptom onset for each of the various body fluid specimen types.

• EBOV presence, measured both as detected RNA and isolated virus, in any of the relevant body fluids, will be analyzed in relation to time of persistence.

• Analysis of RNA derived from selected specimens collected during the study will include genetic analysis and comparison with Ebola virus sequences derived from the participant. This will include sequences characterized during the acute phase of EVD (if available) and comparison with other Ebola virus sequences that have already been characterized. This will help to better describe the variation in virus sequence over time within individuals.

• Viral persistence in a body fluid at a certain period in time, will be analyzed in relation to host factors such as age, sex, co-morbidity including HIV and its clinical characteristics, severity of the earlier Ebola infection and Ebola sequelae, as well as presence and titers of IgM and IgG antibodies in serum. Information on exposure to experimental treatment or vaccination will also be taken into account in the analysis.

• Participant information on sexual history will be analyzed for frequency and type of

(protected/unprotected/vaginal/oral/anal) sex.

• The calculation of correlation between positive RT-PCR and culture tests for each body fluid specimen types will be performed, conditioned upon time since the first convalescent negative RT-PCR blood test.

• ETU CRFs will be accessed retrospectively to investigate clinical severity of disease and so on. Currently we do not know what the quality of the data in the ETU CRFs will be, as they have not been accessed. Where ETU records do exist for study participants, there may be inconsistency in the data collected between the ETU CRFs and the study questionnaires. The ETU CRFs will primarily be used to add additional information that the participant may not have been able to recall; and verify data that has been collected in the corresponding section of the questionnaire. In cases where there are discrepancies with what is recorded in the questionnaire and the ETU CRFs, additional weight will be given to data captured in the questionnaire. The data capture for the study questionnaires is conducted by designated, trained team members and is therefore standardised. Data collected in ETU CRFs is likely to have varied between ETUs and is likely to have been collected in a less uniform way (unknown amount of training of staff, likely to have been collected by a large pool of staff and so on.

- 3 and 6 month visit body fluid RT-PCR test results will be analyzed to describe if body fluid specimens can test positive after two consecutive negative test results. A descriptive analysis of the questionnaire will be performed to assess any clinical complaints or health events, and to compare them to previous test results for any correlation of complications related to previously detected virus persistence.
- Outcomes of pregnancy will be described and related to the participant’s previous test results.

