**Project summary**

Little is known about the post-recovery persistence of Ebola virus (EBOV) and the risks of transmission from convalescent Ebola survivors during close or intimate contact. During this ongoing outbreak, it is important to fully understand how long the virus stays active in body fluids other than blood in order to reduce transmission and also which host factors determine persistence. Thus, we propose to investigate the persistence of the virus in different body fluids and its relation to immune response in a cohort of survivors, in order to target and refine public health interventions to arrest ongoing spread of disease. This will be an observational cohort study including survivors at different points of convalescence. Results and analyses will be used to update relevant counseling messages and recommendations from the Ministry of Health and Sanitation (MoHS), WHO, and US-CDC.

The study will be comprised of a pilot and a main study including specimens from adult men and women (serum, semen, vaginal secretions, and saliva, tears, sweat, urine, rectal swab, menstrual blood and breast milk if applicable), Participants will be recruited from Ebola treatment units (ETUs) and survivor registries and special efforts will be made to recruit HIV positive survivors. Participants in the study will be followed up at study sites in government hospitals.

Specimens will be tested for EBOV RNA by RT-PCR in Sierra Leone at 2-4 week intervals and the positive RT-PCR samples will be sent to US-CDC Atlanta for virus isolation. Each body fluid will be collected until two negative RT-PCR results at 2 weeks interval are obtained. Participants will be followed until all studied body fluids are negative. Analyses of antibody response, including titers of IgM and IgG, will be repeated in parallel to the body fluid tests.

Pilot and main study participants will be offered a follow-up visit with a questionnaire and body fluid testing at 3 and 6 months after their second negative RT-PCR test result.

Pregnant women will have an additional follow up to document the evolution of pregnancy, the outcomes of delivery, including products of delivery and body fluid testing. The process of this follow-up is detailed in the annex to this protocol

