***1.2.4 Specific objectives of Main study:***

**Main study: Persistence of Ebola virus in semen, vaginal secretions and other body fluids among EVD survivors**

• In 1st /baseline specimen samples, to assess period prevalence of:

a) presence of Ebola RNA detected by RT-PCR

b) of live Ebola virus detected by culture/viral isolation in: i) semen, ii) vaginal swab, iii) rectal swab, iv) sweat, v) urine, vi) saliva, and vii) tears, viii) menstrual blood and ix) breast milk, if applicable.

• To assess the maximum duration of:

a) any Ebola ribonucleic acid (RNA) detected by RT-PCR and

b) of live Ebola virus detected by culture/viral isolation in: i) semen, ii) vaginal swab, iii) rectal swab, iv) sweat, v) urine, vi) saliva, and vii) tears, viii) menstrual blood and ix) breast milk if applicable.

• To analyse the survival function, including survival probabilities (probabilities of virus persisting) at key time points, using RT-PCR and viral isolation results among individuals with specimens that are positive by RT-PCR at the baseline visit, and with subsequent specimens collected until RT–PCR and virus isolation are confirmed negative.

• To inform maximum duration of persistence in semen and to estimate a period prevalence of viral persistence in semen of survivors 12-15 months post disease onset. (‘Tail-end cohort’).

• Describe concordance between RT-PCR (including CT-values) and viral culture results for EBOV in these body fluids.

• To analyze viral persistence in relation to host factors (socio-demographics, behavioral variables, Ebola disease course and severity, other diseases including HIV, reproductive health including pregnancy, and humoral immune response.)

- To describe outcomes of pregnancy and delivery in pregnant participants (detailed in annex to the protocol)

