***Sample size calculations***

**Pilot study sample size:**

A maximum of 100 men (not based on sample size calculations in relation to power, but on feasibility for assessing study process and generating enough knowledge for main study) will be included with a target of 40% between 2 and 3 months convalescence period and 60% with over 3 months convalescence period. These men will be followed until they have provided two consecutive negative semen specimens within a 2 – 4 week interval, and may be merged with the main study cohort as needed.

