**1. 60 men and 60 women (50+20% drop-out) should hence be included, in each of the study sites (Freetown and Porto Loko.)**

In order to maximize the possibility of detecting virus RNA in body fluid specimens, the lag time since symptom onset should be pushed towards recent survival (3 months post discharge or less). If male or female survivors with <= 3 months since discharge cannot be identified, the lag time may need to be postponed until 6 months post discharge. Male survivors from the pilot study may be invited for this purpose, for additional body fluid testing, but would need to be drawn from a random list of pilot participants, giving semen negative men an equal probability as semen positive to participate.

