**Specimen Collection Main study**

1. Specimen collection will take place in designated areas of the study clinic, in a special room designated for this purpose. The study technician will label and mark all specimen containers before collecting, with the participant’s personal ID number, study name, visit number, date, specimen description and name of clinic. All specimen collection will follow guidelines; see further details in operations manual.

2. Blood, sweat, tears and saliva will be collected by a trained healthcare worker. Breast milk, vaginal swab (for vaginal secretions and menstrual blood) and rectal swab can either be self-collected, or collected by a gender appropriate, trained healthcare worker. Semen and urine will be self-collected by the participant using low- literacy illustrated instruction cards and detailed verbal instructions from the trained healthcare worker. Specimens placed on a designated counter in the private room. A trained healthcare worker (well informed of the SOP and trained in infection control procedures and wearing adapted personal protection equipment (face mask, apron, gloves, and boots) against potential contaminated fluids) will then enter the room and seal the container with the specimen respecting all infection control procedures.

3. Serum will be collected by a trained healthcare worker, the procedure aligned with standard practice for infection control.

4. For male participants, urine should be collected prior to semen specimen collection to prevent the risk of contamination.

5. Collection of the different specimens will follow standard operating procedures (Outlined in operations manual).

Specimen projections by visit, MEN 1-3 months post EVD symptom onset:

|  | **Blood** | **Semen** | **Saliva** | **Tears** | **Urine** | **Sweat** | **Rectal** | **TOTAL** |
| --- | --- | --- | --- | --- | --- | --- | --- | --- |
| **Visit 1** | 120 | 120 | 120 | 120 | 120 | 120 | 120 | 840 |
| **Visit 2** | 120 | 120 | 120 | 120 | 120 | 120 | 120 | 840 |
| **Visit 3** | 120 | 120 | 120 | 120 | 120 | 120 | 120 | 840 |
| **TOTAL** | 360 | 360 | 360 | 360 | 360 | 360 | 360 | 2520 |

Specimen projections by visit, WOMEN 1-3 months post EVD symptom onset:

|  | **Blood** | **Vaginal OR Menstrual Blood** | **Saliva** | **Tears** | **Urine** | **Sweat** | **Rectal** | **Breast Milk** | **TOTAL** |
| --- | --- | --- | --- | --- | --- | --- | --- | --- | --- |
| **Visit 1** | 120 | 120 | 120 | 120 | 120 | 120 | 120 | ? | 840 |

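### The survival curve uses only baseline RT-PCR positives but is timed from symptom onset with no delayed-entry rule, so a standard curve overstates persistence, mainly for semen

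*Combined protocol and SAP*

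**What the plan says.** Section 7 (Data analysis plan) lists three primary measures. One is "survival probabilities over time (based on base-line positive samples". Section 1.2.4 sets the same restriction: the survival function is to be estimated "among individuals with specimens that are positive by RT-PCR at the baseline visit". Section 7 fixes the clock: "Viral Persistence time will be measured in days or months from time after symptom onset and will also be presented as time after ETU discharge".

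Entry comes after both of those origins for anyone recruited from a registry, and it varies:

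- The Project summary says "This will be an observational cohort study including survivors at different points of convalescence".
- The main-study sample-size table gives 0 to 3 months after onset. The specimen projections are headed "MEN 1-3 months post EVD symptom onset".
- If recent survivors cannot be found, "the lag time may need to be postponed until 6 months post discharge".
- HIV-positive survivors form a separate sub-cohort, taken regardless of time since discharge.
- The pilot targets 40% of men at 2 to 3 months and 60% beyond 3 months. These men "may be merged with the main study cohort as needed".

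The documents name no estimator for the curve. They do not mention delayed entry, left truncation, or left or interval censoring, and they give no rule for dating clearance. Participants negative at baseline appear in another primary measure, the period prevalence in first samples by time band, but not in the survival function.

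**The concern.** A survivor who cleared the virus before the first visit cannot enter this curve. Everyone in it is therefore known to be still positive up to enrolment. If the clock nevertheless starts at onset and each person is counted at risk from that point, the time before enrolment is guaranteed event-free time and the curve sits too high. This is left truncation from prevalent sampling.

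The probability of virus persisting at key times is meant to feed counselling and recommendations (Project summary; Section 14), and survivors want to know when intimacy is safe (Sections 1.1 and 11.1). Section 1.1 also describes male survivors being confined and stigmatised, so overstated persistence is not a harmless error on the cautious side.

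The bias also depends on when people enrolled. Groups with the same true persistence but different entry times would give different curves. That matters because the null hypothesis refers to persistence time by HIV status, and HIV-positive survivors are enrolled without the time limit set for the main cohort.

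**Working it through.** **The plan's own figures.** None is given for this curve. The only computed figures, the zero-numerator bounds (7.1% for 50, 3.6% for 100), do not enter it.

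**Inputs.** From the documents: the restriction to baseline positives, the onset clock and the entry windows above. Assumed, because the documents give no clearance distribution: exponential clearance, entry spread evenly over a window, and entry time independent of clearance time.

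**Formula.** Let S(t) be true persistence from onset and A the entry time. A curve on baseline positives, with all counted at risk from time 0, estimates

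E[S(max(t, A))] / E[S(A)].

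The denominator is the baseline prevalence. For t beyond the last entry time this becomes S(t) / (baseline prevalence).

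**Direction.** S(max(t, A)) is the smaller of S(t) and S(A), and the smaller of two probabilities is never below their product. So the ratio is never below S(t), whatever the distribution, provided entry and clearance times are independent. It is strictly above S(t) beyond the last entry time if anyone cleared before entry.

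**Main illustration: median 4 months, entry at 0.5 to 3 months.**

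- Rate = ln 2 / 4 = 0.1733 per month.
- S(0.5) = 0.917, S(3) = 0.595, S(6) = 0.354.
- Baseline prevalence = (0.917 − 0.595) / (0.1733 × 2.5) = 0.744.
- Curve at 3 months = 0.595 / 0.744 = 0.80, against a true 0.59.
- Curve at 6 months = 0.354 / 0.744 = 0.48, against a true 0.35.
- Median read from the curve = −ln(0.5 × 0.744) / 0.1733 = 5.7 months, against 4.

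These figures are truncation alone. Dating clearance to the first negative of two-weekly visits would raise them, in simulation, to about 0.83 and just under 0.50.

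**Range over other medians, entry at 1 to 3 months.**

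| True median (months) | Baseline prevalence | Factor | True S(6) | Curve at 6 months |
| --- | --- | --- | --- | --- |
| 1 | 27% | 3.7 | 1.6% | 5.8% |
| 2 | 51% | 2.0 | 12.5% | 24.5% |
| 4 | 71% | 1.4 | 35.4% | 49.7% |
| 6 | 80% | 1.26 | 50.0% | 62.9% |

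**Delayed entry on the same positives.** Counting each person at risk only from enrolment gives S(t)/S(0.5) in the main illustration: 0.595/0.917 = 0.65 and 0.354/0.917 = 0.39. Most of the excess goes. What remains is the conditioning on being positive at the earliest entry time.

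**Entry timing mistaken for a group effect.** With a true median of 4 months in both groups, the curve at 6 months reads 0.50 for entry at 1 to 3 months and 0.75 for an assumed entry at 1 to 12 months.

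**Using the baseline negatives.** In simulated cohorts of 100, entry at 0.5 to 3 months and an error-free test, a Turnbull estimate with baseline negatives left-censored gave 0.59 and 0.34, against a true 0.59 and 0.35.

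**The case against.** The strongest reply is that the plan names no estimator. An analyst could use delayed entry on the same participants, which the text does not exclude, and most of the bias would disappear. This stands, and it limits the charge: the upward bias belongs to a standard curve run on the text as it is, not to a method the plan has chosen. But the plan does not ask for delayed entry, and a delayed-entry curve would still need a label saying that it is conditional.

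The restriction is also openly stated, so the curve might be called conditional by design. That helps little on an onset clock, because each person is conditioned on being positive at a different time.

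Other parts of the reply also stand:

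- The first primary measure keeps every baseline negative and is unaffected. A reader might infer that all the persistence results are overstated; the documents do not support that.
- A reader might infer equal harm for every fluid. The sample-size section expects prevalence near zero in fluids other than semen, so few baseline positives are likely there.
- A reader might infer that anyone can enter at any time. Only the HIV-positive sub-cohort has no time limit, and it is kept separate. The pilot has stated targets, and merging it is optional.
- Left-censoring on a single baseline negative would conflict with the protocol's rule of two consecutive negatives (2.2.2), with the re-sampling of negatives at visit 2 (Main study structure) and with the intermittent semen shedding that Section 2 anticipates. If one test caught 80% of true persisters (an assumption), persistence at 6 months would fall from 0.35 to about 0.35 × 0.8 = 0.28. The fix must use confirmed negatives.

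**Conclusion.** The point holds for one of the three primary measures, and mainly for semen. A baseline-positive curve timed from onset without delayed entry overstates persistence, by one over the baseline prevalence beyond the last entry time. The direction requires only that some survivors clear before entry and that entry time is independent of clearance time. The size cannot be fixed from the documents. In the illustrations the factor runs from 1.26 to 3.7 for true medians of 6 down to 1 month. In the main one the curve reads 0.80 and 0.48 at 3 and 6 months instead of 0.59 and 0.35.

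It would go too far to say that the plan has committed itself to these biased figures, or to a rule that dates clearance to the first negative visit. It is silent on both the risk set and the dating of clearance. That silence should be filled before the curve is used for guidance.

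**What to change.** In Sections 1.2.4 and 7, estimate time from symptom onset to clearance, per fluid, in all participants with a valid baseline specimen. Use an interval-censored estimator (Turnbull or parametric) and the protocol's definition of two consecutive negatives:

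- Baseline negative, confirmed at visit 2: left-censored at visit 1.
- Baseline negative, positive at visit 2: not yet cleared at visit 2, then followed like any other positive.
- Cleared during follow-up: interval-censored between the last positive and the first of the two confirming negatives.
- Not confirmed negative: right-censored at the last positive.
- A single baseline negative with no second test has no positive to censor at and is uninformative under this definition. Include it as left-censored in a sensitivity analysis.

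If the baseline-positive curve is kept, use delayed entry at the enrolment time and label it as conditional on still being positive at the earliest entry time. Report the entry-time distribution beside any comparison between groups.

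The cost is wording and a standard software routine. No new data are needed, provided that the visit 2 re-sampling of baseline negatives is carried out for everyone. The estimand becomes the proportion of all survivors still positive at time t, so those who never shed count as already negative. Intermittent shedding may misclassify some participants. A sensitivity analysis should address this, for example one that reclassifies participants who test positive again at the 3- or 6-month visit.
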